## Abstract

**Background:**

Acute scaphoid fractures are common in active adults and do lead to reasonable time lost to work. One important goal of treatment is early return to work or sport. On this background, the adequate treatment of non-displaced acute scaphoid fractures is still under discussion. The aim of this study is to compare time to return to previous activity level comparing surgical versus non-surgical treatment of non-displaced acute scaphoid fractures.

**Methods/Design:**

The study is designed as a non-randomized multiple center cohort study including 12 sites in Germany and Austria. The inclusion period is planned to be 12 months with a follow up of 6 months. Allocation to operative or non-operative treatment is choosen by the patient together with his treating surgeon. The primary outcome is time to return to previous activity level adapted for loading of the wrist in daily life as measured by a newly developed questionnaire (PLDL-wrist). Factors identified a priori to be associated with the outcome, e.g., poverty status, age, education, smoking status, gender, and occupation, are measured to ensure adequate control for their potential confounding effects.

**Discussion:**

The rationale and the design of a multiple center cohort study are presented. As it is not considered feasible to randomize patients in this study, potential confounding effects need to be controlled adequately.

## Background

Acute scaphoid fractures mainly occur in active adults, many of whom work as laborers or are involved in competitive athletics; therefore, returning to work or sport is an important goal of treatment. They are the most common fractures of the carpal bones. Time to union of acute scaphoid fractures ranges from 6 to 18 weeks depending on fracture type, localization of the fracture, degree of displacement, and additional soft tissue injury [1-4].

Cast immobilization remains the standard treatment despite the fact that about 20% of fractures fail to heal with conservative treatment[1,5,6]. It is well documented that the rate of nonunion of acute scaphoid fractures is higher for proximal and dislocated fracture types [7-10]. In displaced scaphoid fractures, the nonunion rate rises up to 46%. Advances in the technique and in implants developed for the operative fixation of acute scaphoid fractures have made it technically easier with a higher rate of union [5,11-16]. Operative treatment is recommended for all displaced, unstable and complex fracture types [2,5,13-15,17-20]. In non-displaced acute scaphoid fractures treated by limited access and screw fixation the union rate has been reported as high as 100% [4,5,11-14,21].

The adequate treatment of non-displaced acute scaphoid fractures is still under discussion. A few prospective studies with a limited number of patients and imprecise definitions of fracture type and union were published in 2000 and 2001 [11,12,16]. Despite favoring screw fixation, two recent randomized controlled trials (RCTs) that used 'return to work' (RTW) as an outcome [12,22] did not provide a clear definition or did not define who determined return to work. Neither study administered a patient-derived quality of life measure specific to the wrist like the Disability of the Arm, Shoulder and Hand (DASH) questionnaire [23-25]. In the Cochrane library, there are no systematic reviews or meta-analyses on the treatment of acute scaphoid fractures. Considering the problems associated with prolonged cast immobilization, the complications of non-operative fracture treatment and social/economic factors, it seems appropriate to evaluate the possible advantages of routine operative treatment with a less invasive screw fixation technique for non-displaced acute scaphoid fractures.

The determination of RTW is of growing importance as an outcome in clinical studies in the field of trauma and orthopedic surgery and its application has increased in recent years (Figure 1). One limitation of this outcome is, however, that return to work is applicable for employees only what implies, that RTW cannot be measured in e.g., students, housewifes and -men, unemployed or retired. Also, a wide range of definitions of RTW can be found throughout the literature. The different concepts of RTW have been devided into three groups [26]: (1) Cumulatively, counting all days lost from work beginning with the date of injury, (2) categorically, e.g., RTW ever (yes/no); working at time × (yes/no) or (3) continuously, as time-to-RTW. These concepts have in common, that no information is given nor is any adjustment made for, whether the physical load after RTW differs from the load before the event observed. Therefore, no conclusions can be drawn, whether any functional limitations after RTW are present. To overcome the described limitations in the context of this study, an additional instrument was needed to adapt the outcome RTW and expand its meaning to determine the physical load in daily life, including work and household duties as well as leisure time.

We implemented a prospective cohort study to compare patients with non-displaced scaphoid fractures undergoing operative treatment with those who have non-operative care, addressing several questions: Is the time to return to previous activity level different between those undergoing surgery and those treated non-operatively? In addition, it will be determined whether any differences in treatment outcomes, including functional status as derived from the DASH and SF-36 [27-31], complication rate, range of motion, grip strength, and patient evaluation of pain and overall satisfaction can be seen between the patient groups. Such knowledge could support surgeons and patients in finding an adequate treatment decision.

Finally, cost-effectiveness of surgical versus non-surgical treatment will be evaluated, focusing on direct, as well as indirect costs of treatment and social/economic factors.

## Methods/Design

We designed a multi-center prospective cohort study of patients with complete, non-displaced scaphoid fractures receiving either operative or non-operative treatment to compare the time to return to daily activities. The inclusion period will be approximately 12 months. Follow-up examinations (Figure 2) are planned at 6-weeks, 3-months and 6-months following onset of treatment. Additionally, telephone interviews are planned at 3-, 9- and 15 weeks.

The clinical investigational plan was approved by the ethics committee of the Medical Faculty of Philipps-University Marburg.

### Study design

The study is designed as a non-randomized cohort study, involving multiple sites with multiple surgeons and potentially differing patient populations. The chosen design implies a potential for bias and uncontrolled confounding. This will be addressed in the method of data collection and data analysis (see below). The eligibility criteria do only allow patients to be included, that do have isolated, complete fractures of the mid third of the scaphoid without signs of displacement or comminution visible in CT scan, while patients with any additional fracture of other sites are excluded, leading to a very homogenous injury pattern an thus minimizing residual "confounding by indication".

### Patients

Adult patients with isolated, acute (no more than 2 weeks between injury and treatment) complete fracture of the mid third of the scaphoid, without any signs of displacement or comminution visible in CT scan, are eligible for this study. Patients meeting the inclusion and exclusion criteria (Table 1) are identified by the participating centers and will be informed about the study. Patients are recruited from 10 clinics in Germany and 2 clinics in Austria (Table 2). All patients need to sign an informed consent form before entering the study.

### Treatment allocation

The decision on whether to choose an operative or non-operative treatment procedure is taken by the patient together with his treating surgeon. The participation in the study is completely independent of this decision and does not influence the choice of treatment procedure. Patients are classified as operative or non-operative according to the initial treatment decision taken during the first two weeks following injury.

### Interventions

Operative treatment (Group A) will be performed using minimally invasive palmar or dorsal access. Retrograde as well as antegrade screw insertion is up to the choice of the performing surgeon. The fracture fixation is done in free hand technique, using a cannulated screw. Postoperative splint immobilization should not exceed 1 week.

Non-operative treatment (Group B) will be performed with short arm plaster cast including first carpo-metacarpal joint but leaving first metacarpal-phalangeal joint and all fingers free. Immobilization for 6 weeks is recommended, further immobilization if necessary.

Patients in both groups are supposed to receive 10 sessions of physical therapy.

### Outcome assessment

This study focuses on differences in time to return to daily activities and patient derived quality of life instruments between the two groups. These outcome parameters will be assessed by means of questionnaires.

### Primary outcome measures

(1) Questionnaire on physical loading of the wrist in daily life (PLDL-wrist). The PLDL-wrist (Additional file 1: German version, Additional file 2: English translation) is a newly developed 17-item questionnaire, based on the German translation of the DMQ [32]. Each of the items can be answered by either 'YES' or 'NO', leading to a maximum score of 17. At baseline all patients will be interviewed to get the baseline PLDL-score of the last week before the injury. t_0_, being defined as the day of onset of treatment, will be given the baseline PLDL-score. The questionnaire will be repeated at several follow-ups according to the schedule in Figure 2. The individual score at every interview will be expressed as a percentage of the baseline score (PLDL_xweeks_/PLDL_Baseline _* 100) and plotted over time. The endpoint is defined as 'Time to reach the individual 80%-threshold'. To determine the time point at which the 80%-threshold is reached, the change between the first score value exceeding the 80%-threshold and the prior score value is linearized. The intercept of this line and the 80%-threshold represents the linear estimation of the first day of return to previous activity level (t_return_).

(2) Questionnaire on the activity status (QAS). The QAS differentiates between the categories (A) return to work [full; partly; no; not applicable], (B) return to household duties [full, partly, no] and (C) return to leisure activities [full, partly, no]. Using the QAS will allow us to include patients who are not formally employed (e.g. students, housewives and -men, self- or unemployed). At baseline all patients will be asked for their activity status in the last week before the injury. This will be repeated according to the schedule in Figure 2. A patient has returned to previous activity level either when he or she has returned to full work **and** returned to full household duties or – for those not being employed – has returned to full household duties only. Rates of return to previous activity level will be calculated for each of the follow-up periods. Leisure activities are not included in this definition; these are evaluated as secondary outcomes, however.

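### Primary outcome (1) is named as reaching 80% of the baseline PLDL score but is derived from the first score above 80%; the two differ at baselines 5, 10 and 15

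*Protocol article*

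**What the plan says.** All of the relevant text is in the Protocol article, Primary outcome measures, item (1).

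- The scale: "Each of the items can be answered by either 'YES' or 'NO', leading to a maximum score of 17".
- The denominator: "At baseline all patients will be interviewed to get the baseline PLDL-score of the last week before the injury".
- The ratio: "The individual score at every interview will be expressed as a percentage of the baseline score".
- The endpoint by name: "Time to reach the individual 80%-threshold".
- The rule that finds it: "the change between the first score value exceeding the 80%-threshold and the prior score value is linearized".
- The date recorded: "The intercept of this line and the 80%-threshold represents the linear estimation of the first day of return to previous activity level".

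The name is satisfied by a score equal to the threshold. The rule needs a score greater than it. The section as shown gives no rule for a baseline score of 0.

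**The concern.** On a continuous scale the difference between reaching and exceeding a threshold hardly matters. Here the score is a whole number and the threshold is a simple fraction of another whole number, so exact equality is a real outcome. A patient can be at the threshold by the endpoint's name and not yet at it by the endpoint's rule. The recorded time then depends on which sentence the analyst follows, and for some patients so does whether any time is recorded. This is a primary outcome, and the sample size is planned on a comparison of its mean, so the definition should give one answer.

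**Working it through.** **The plan's own figure.** The Sample size calculation section uses a two-sided t-test, alpha 0.05, power 90%, a difference of 4 weeks, an SD of 5 weeks, a 1:4 ratio of cast to screw, and 25% loss.

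n(cast) = (1 + 1/4) × (1.960 + 1.282)² × 5²/4² = 1.25 × 10.51 × 1.5625 = 20.5, rounded up to 21, with 4 × 21 = 84 screw patients. Allowing for loss: 21/0.75 = 28 and 84/0.75 = 112. This reproduces the stated 28 and 112, and nothing below changes it.

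**Where the two wordings differ.** For baseline B, the rule needs the smallest whole number k with k > 0.8B; the name needs the smallest k with k ≥ 0.8B. These differ only when 0.8B is a whole number, that is, when B is a multiple of 5.

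| Baseline | Score needed, exceeding 80% | Score needed, reaching 80% |
|---|---|---|
| 5 | 5 (100%) | 4 (80%) |
| 10 | 9 (90%) | 8 (80%) |
| 15 | 13 (86.7%) | 12 (80%) |
| all others from 1 to 17 | same | same |

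**What this does to the recorded time.** Assumptions:

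- The PLDL is collected at all contacts listed under Methods/Design (the schedule figure is not shown), with 3 and 6 months taken as weeks 13 and 26.
- The rule is applied to scores after t0, because t0 itself carries the baseline score and is 100% by construction.

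The interpolated time is t = t(prior) + (80 − prior%) × (interval)/(current% − prior%). Take baseline 10, with scores of 2 at week 3, 4 at week 6 and 8 at week 9. In every case below, the at-or-above rule gives 6 + (80 − 40) × 3/(80 − 40) = week 9.

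| Scores at weeks 13, 15, 26 | Time under the written rule |
|---|---|
| 9, 10, 10 | 9 + 0 × 4/10 = week 9 (no difference) |
| 8, 8, 9 | 15 + 0 × 11/10 = week 15 (6 weeks later) |
| 6, 9, 10 | 13 + 20 × 2/30 = week 14.3 (5.3 weeks later) |
| 8, 8, 8 | no event |
| 6, 6, 6 | no event |

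**Size at group level.** One 6-week shift moves a mean of 21 cast patients by 6/21 = 0.29 weeks, and a mean of 84 screw patients by 6/84 = 0.07 weeks. The planned difference is 4 weeks.

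**Baseline 0.** If each YES counts one point (the minimum is not stated), 0 is a possible score, and the percentage is then a division by zero.

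**The case against.** The strongest defence is that the interpolation largely repairs the wording. When a score of exactly 80% is followed by a higher one, the line meets the threshold at the exact-80% visit, so both wordings give the same date. That stands. A reader might infer that patients at exactly 80% are generally missed. They are not: only those at baselines 5, 10 and 15 who then plateau or decline are affected.

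A reader might also infer that low-baseline patients are held to full recovery. At baselines 1 to 4 a score of 100% is needed under either wording, simply because the score is a whole number; only baseline 5 depends on the word *exceeding*. Even then, 100% is the score that triggers the event, and the recorded time is still interpolated back to 80%.

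Nor do the documents show that low baselines are common or differ between the groups. The Background describes mainly active adults and says the instrument covers work, household and leisure, so not being employed does not imply a low score. Occupation is among the confounders named in the abstract, and the Data analysis section adjusts the outcomes for such factors in the secondary analysis.

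It can also be said that an article leaves such details to the full protocol or SAP. That is fair for baseline 0, where an analyst would fill the gap. It does not answer the main point, because the article itself fixes both the name and the rule, and they disagree.

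**Conclusion.** The concern holds in a narrow form. Item (1) sets two criteria for the same event. They conflict at three baseline scores, and the written rule gives a late event or none to a patient who reaches the threshold there and then plateaus or falls back. For such a patient the delay in the worked examples is 5.3 to 6 weeks, which is more than the planned 4-week difference. The effect on a group mean is small unless several patients are affected. The number affected is unknown and could be nil, since no baseline distribution is given. No direction of bias between the groups can be claimed. The conclusion assumes one point per YES and scores at every listed contact. The stated sample size is not in question.

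**What to change.** Reword the derivation so that it starts from the first follow-up score at or above the 80% threshold. This matches the endpoint's name. The prior follow-up score is then always below 80%, so the line between two follow-up scores crosses the threshold once, no later than the triggering visit.

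As a minor accompanying clarification, add that the percentage is undefined at a baseline score of 0. Such patients, if any, have no value for outcome (1) and contribute to the QAS and the secondary outcomes.

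The cost is two sentences, with no new data and no change to 112 + 28. A minimum baseline score, such as 5, is not recommended. It would remove enrolled patients from a primary outcome planned on exactly 21 evaluable cast patients, sit uneasily with the intention-to-treat statement, and still leave required scores running from 80% to 88.9% (8 of 9 at baseline 9).

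### The QAS event for 'return to previous activity level' is not tied to pre-injury status and differs by employment, leaving the unstratified primary comparison open to any employment imbalance

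*Protocol article*

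**What the plan says.** Under Primary outcome measures, item (2), the protocol article defines the QAS event. For employed patients: "A patient has returned to previous activity level either when he or she has returned to full work", together with full household duties. For patients who are not employed, the event is met when the patient "has returned to full household duties only". Leisure is left out: "Leisure activities are not included in this definition".

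The work item has four answers, "A) return to work [full; partly; no; not applicable"; household duties have the first three only. On baseline data the section states: "At baseline all patients will be asked for their activity status in the last week before the injury".

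The same item explains whom the questionnaire lets the study include: "Using the QAS will allow us to include patients who are not formally employed (e.g. students, housewives and -men, self- or unemployed".

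Three other sections bear on this. Treatment allocation leaves the choice of treatment to the patient and surgeon. Sample size calculation sizes outcome (2) on a two-sided log-rank test with 86 and 30 patients and mentions no strata. Data analysis places adjustment for baseline confounders in the secondary analysis.

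**The concern.** Three features of one stated rule need attention.

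- **No link to baseline.** The outcome is about regaining a previous level, and that level is recorded, yet the event asks for 'full' without referring to it. A patient who did only part of the household work before injury has no clear route to the event.
- **An unsettled group.** The self-employed are listed among those not formally employed. The household-only rule is written for those not being employed. The two terms are not reconciled, so it is unclear whether a self-employed person must return to work to count.
- **Two events pooled as one.** Employed patients need work and household duties; others need household duties only. For the same recovery, the two-part event cannot come earlier than its household part.

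At stake is a primary comparison in a non-randomised study. If the arms differ in employment mix, the curves can separate, or a real separation can shrink, without any treatment effect.

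**Working it through.** **1. The plan's own figure.** The stated power for outcome (2) is about 92% at 86 and 30 patients. It rests on the survival rates in Table 3, which are not in the text at hand, so it cannot be reproduced. This point does not claim it is wrong.

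**2. Baseline anchoring, side by side.**

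| Endpoint | Baseline collected? | Baseline used in the event? |
|---|---|---|
| (1) PLDL-wrist | yes | yes: "The individual score at every interview will be expressed as a percentage of the baseline score" |
| (2) QAS | yes | not mentioned |

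The Background section criticises return-to-work outcomes for not adjusting for load before the event. The Sample size calculation section criticises two earlier randomised trials because activity after the trauma was not compared with activity before it. The QAS rule, as written, leaves the same gap.

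If 'full' is read literally and a share q of patients was at 'partly' before injury, at most 1 − q can meet the event by regaining their prior level: 95%, 90% and 80% for q = 5%, 10% and 20%. These values of q are assumptions; the documents give none.

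**3. Effect of pooling one-part and two-part events.** Assume no treatment effect. At a given visit let h be the share at full household duties, w the share of those who are also at full work, and f the share of an arm judged on household duties only. Then

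return rate = h × [f + (1 − f) × w]

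and the spurious difference between arms is h × (1 − w) × (f_A − f_B).

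All inputs are assumed: h = 0.8, w = 0.6 or 0.8.

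| w | f_A | f_B | Rate A | Rate B | A − B |
|---|---|---|---|---|---|
| 0.6 | 0.20 | 0.20 | 54.4% | 54.4% | 0 |
| 0.6 | 0.10 | 0.30 | 51.2% | 57.6% | −6.4 points |
| 0.8 | 0.20 | 0.20 | 67.2% | 67.2% | 0 |
| 0.8 | 0.10 | 0.30 | 65.6% | 68.8% | −3.2 points |

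For example, with w = 0.6: 0.8 × [0.10 + 0.90 × 0.6] = 0.512 and 0.8 × [0.30 + 0.70 × 0.6] = 0.576. Swapping the shares reverses the sign, so the bias can favour either arm. In a cast group of 30, 20 percentage points is 0.20 × 30 = 6 patients.

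**The case against.** The strongest reply is that the answers grade a return. 'Full' may therefore already mean full relative to before the injury, and a part-time worker back at all prior duties would qualify. The questionnaire's item wording is not in the text, so this reading cannot be excluded. It sits awkwardly with asking the same item about the week before injury, when every patient would answer 'full' by definition. The rule is ambiguous, and a primary endpoint should not be.

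Second, a reader might infer that the self-employed are certainly counted on household duties alone. The documents do not establish this. The sentence that lists them describes who can be included, not which rule applies, and a working self-employed person could answer the work item. The Background section points both ways: it limits return to work to employees, but its examples of people in whom it cannot be measured do not include the self-employed. What stands is that two terms need reconciling.

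Third, the one-part rule is a deliberate way to include people without paid work, and some asymmetry is unavoidable. That is correct. Redefining the event keeps the asymmetry; only stratification keeps it out of the treatment comparison. Stratification is often left to an analysis plan, but here the article itself fixes the event and places adjustment in the secondary analysis.

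Fourth, a reader might infer that employment drives the choice of treatment, so that bias is bound to occur. No section says so. The article names patient and surgeon preferences, and lists occupation as a factor associated with outcome. An imbalance is plausible under self-selection but is not documented.

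**Conclusion.** The concern holds as a defect in how the event is specified. The rule does not use the pre-injury status it collects, does not say where the self-employed belong, and pools two different events by employment. The primary comparison is therefore exposed to any employment imbalance between self-selected arms.

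The size cannot be derived from the documents, which give neither the employment mix nor the distribution of pre-injury status. With an equal mix, pooling creates no spurious difference. The 3.2 to 6.4 points above rest wholly on assumed return rates and an assumed 20-point imbalance. It would be tempting to express the bias as a fraction of the 4-week difference in the sample size section, but that difference belongs to outcome (1), a different endpoint on a different scale, and does not support such a figure. Actual misclassification of patients is possible but not shown.

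**What to change.** 1. Define return on the QAS as regaining at least the patient's own baseline category in each component that counts.
2. State a rule for patients at 'no' on a component at baseline. Without one, they would meet that component at time zero.
3. Require the work criterion for everyone whose baseline work answer is other than 'not applicable', and say explicitly that this includes the self-employed.
4. Stratify the primary QAS log-rank analysis by baseline work applicable (yes/no), so that patients are compared only with others held to the same event.

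The baseline items are already collected, so only the definition and the analysis text change. There are two costs. A two-level stratum loses a little information in a cast group of about 30. And 'partly' is a coarse category: a patient at 'partly' before injury would count as returned at any 'partly' level, even a more limited one. Stratifying by this item does not address confounding by other factors.
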